## **Protection of patient data**

The study will be submitted to the Danish Data Protection Agency. Relevant legislation concerning personal information will be followed.

All information will be treated confidentially and in the reporting of test results, patients will be anonymous and the persons responsible for this trial are bound to confidentiality.

Data collected in the form of a Case Report Form, signed informed consents, and records will only be made available to authorised representatives from relevant authorities, in accordance with Danish law.

# **FRAMEWORK FOR THE STUDY**

## **Schedule**

The study is scheduled to start: 1/5-2014

The study is scheduled for completion: 1/6-2015

## **Location of the study:**

Rigshospitalet

Department of Anaesthesia 4231, HOC, Rigshospitalet.

Pain laboratory.

## **Study Design**

Type of trial: Explorative study

Participants: Healthy volunteers, males, age: 18-35 years.

Number: 50

Randomization: Sequential order of LTS and HPDT will be randomized in accordance with randomization schedule developed by Copenhagen trial unit.

Blinding: Completed psychological tests will be kept in opaque sealed envelopes. The blinding will be broken when all volunteers have completed the four study days.

# **STUDY SELECTION**

## **Inclusion criteria.**

Patients must meet all the following criteria to be suitable for inclusion in the study:

- Age >18 years and <35 years
- Speak and understand Danish
- Male gender
- Study participants who have understood and signed the informed consent
- No prescription medicine during the last 30 days.

## **Exclusion criteria.**

Study participants who meet one or more of the following criteria are not suitable for inclusion in this study:

- Study participants that cannot cooperate to the test.
- Study participants with an alcohol and/or substance abuse, assessed by the investigator
- Study participants with a substance abuse, assessed by the investigator.
- Study participants, who have consumed analgesics less than 2 days before experimental day.
- Study participants, who have consumed antidepressant medication during the last 30 days before experimental day.
- Study participants with chronic pain.
- Study participants with psychiatric diagnoses.
- Study participants with tattoos on the extremities.
- Study participants with a Body Mass Index of >30 kg/m^2^ or <18 kg/m^2^

# **Other**

## **Funding**

This study was investigator-initiated, and implemented by MD [name], and MD [name].

Costs in connection with the study relate to the pay of the study participants as well expenses related to equipment. The participants will receive 150 DKK per hour (1 hour for screening and 2 study days with 1 hour per study day). The pay is taxable. External funding will be applied for in order to cover the expenses related to the study. The funds will be transferred to individual research accounts established specifically to the individual fund. The accounts are subjected to official audit. The study participants will be informed if any external funding is granted.

The investigator is employed at the Department of Anaesthesia 4231, HOC, Rigshospitalet, and has no financial interest in the trial.

## **Participant’s completion of and withdrawal from the trial**

- A study participant who has completed the study is defined as a study participant who has followed the trial's plan for the prescribed 2 study days.
- A study participant who has not completed the study is defined as a participant included in the trial, i.e. who has given informed consent, but did not complete the trial.
- If a study participant does not complete the trial an account should be given as to whether and how this participant is followed in the trial – this also applies to drop-outs – as well as what data has been collected from these participants.

## **Reasons for participant’s withdrawal from the trial**

A study participant can be withdrawn from the trial under the following conditions:

- If the investigator believes that a change of trial plan will be in the best interest of the study participant.
- If the participant wishes to withdraw from the trial.
- Violation of protocol rules.

## **Procedure for participants who withdraw from the trial**

In accordance with the Declaration of Helsinki, study participants have the right to withdraw from the trial at any time for any given reason. The investigator also has the right to withdraw a study participant from the trial at any time.

The reason why a study participant is withdrawn from the trial before the scheduled time shall be recorded in the study participant’s Case Report Form. If the participant will not describe the reason of withdrawal, it will also be recorded in the participants Case Report Form.

# **METHODOLOGY**

## **General procedure**

On the study days all study participants will be tested lying in the supine position. The study will be conducted in a quiet secluded room, where only the study participant and the investigator will be present.

The study participants will be tested with 3 types of pain conditioning on four separate study days. The 3 types of pain conditioning consist of Brief Thermal Sensitisation (BTS), Heat Pain Detection

Threshold (HPDT), and Long Thermal Stimulation (LTS), (see Clinical evaluations). HPDT and LTS are conducted subsequent to BTS. , the order of the stimulations (HPDT and LTS) is randomised for each patient and each experimental day, by a randomisation schedule developed by Copenhagen Trial Unit. Likewise, the investigators/observers responsible for testing and data registration will also be randomised, so the same investigator will not be responsible for 2 consecutive experimental days. There will be 2 different investigators responsible for the testing. The randomisation schedule is stored in sealed and opaque envelopes to secure adequate allocation concealment

The study participants will be tested with three types of pain conditioning on four separate experimental days. Furthermore, the study participants will complete the two psychological tests, PCS and HADS (see Assessments and tests)

The study participants will be tested with the following types of pain conditioning:

1. Brief Thermal Sensitisation (BTS). The test is conducted centrally on the anterior part of the right thigh. BTS will be conducted at the time: 0 min. (see Assessments and tests).
2. Heat pain detection threshold (HPDT). The test is conducted centrally on the anterior part of the dominant lower arm. HPDT (see Assessments and tests) will be conducted at the time: 7 or 10 min. depending on the randomisation (see Randomisation).
3. Long thermal stimulation (LTS). The test is conducted centrally on the anterior part of the non-dominant lower arm. A continuous VAS-measurement will be performed during the test. The test will be conducted at the time: 7 or 10 min. depending on the randomisation (see Randomisation).

The entire study consists of one screening day and four identical study days. The screening and study days will proceed as follows:

Screening day:

- Oral information regarding the project is delivered by the primary investigator. The participant will be given time to consider the information.
- Short medical history by the primary investigator. Thorough screening of in- and exclusion criteria. Measurement of height, weight, blood pressure and pulse.
- In order to familiarise the study participant with the types of pain conditioning, the 3 types of pain conditioning test are presented and performed on the study participant.
- Distribution of PCS and HADS (in Danish), together with an opaque envelope, in which the answered test are to be put, and a sealed envelope will be returned to the primary investigator on the first study day.
- Potentially clarifying questions concerning the study or PCS and HADS are answered.

Study day 1, 2, 3, and 4:

- Inspection of signed informed consent and written authority.
- Returning of the filled in PCS and HADS questionnaires in a sealed opaque envelope to ensure that the investigators cannot access the data prematurely (study day 1). The envelope is opened when the study participant have completed the four experimental days.
- The study participant is placed on a bed in a supine position.
- Commencement of study:
  - 0 min: Brief thermal sensitisation.
  - 7 min: HPDT or LTS (depending on the randomisation)
  - 10 min: HPDT or LTS (depending on the randomisation)

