**Secondary outcomes**

To evaluate how precise the scores of PCS and HADS, total and sub-scores, predict the size of the area of secondary hyperalgesia following brief thermal sensitization.

To evaluate how precise HPDT and pain during 1 min. thermal stimulation of the skin (LTS) predict the size of the area of secondary hyperalgesia following brief thermal sensitization.

The results from this study are to be used in evaluating sample size in future studies.

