**Hospital Anxiety and Depression scale (HADS)**

HADS is a questionnaire consisting of 14 questions, and is a 4-point Likert scale with values from 0-3. HADS can be subdivided into HADS-A, evaluating anxiety, and HADS-D, evaluating depression. The highest achievable score is 42, and a total HADS-score will estimate the participant’s level of distress. To evaluate anxiety and depression separately, HADS-A and HADS-D must be evaluated separately, with a maximum score of 21 in the two subtests (20).

The interpretation of the score in HADS-A and HADS-D is as follows:

- 0-7: Normal
- 8: Mild level of anxiety/depression
- 11-15: Moderate level of anxiety/depression
- >16: Severe level of anxiety/depression

The HADS questionnaire is to be completed before study day 1.

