**Pain Catastrophizing Scale (PCS)**

PCS is a questionnaire consisting of 13 questions. PCS is a 5-point Likert scale with values from 0-4, and can be subdivided into 3 subtests, that each evaluates the central elements in catastrophizing: Rumination, magnification and helplessness. The highest achievable score is 52, and with separate evaluation of the three subtests, the 3 different elements can be assessed individually. To evaluate the 3 elements separately the 13 questions must be evaluated in the 3 following subgroups:

- Rumination: The sum of question 8, 9, 10, 11. Maximal sum =16
- Magnification: The sum of question 6, 7, 13. Maximal sum = 12
- Helplessness: The sum of question 1, 2, 3, 4, 5, 12. Maximal sum = 24

The PCS questionnaire is to be completed before study day 1.

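### PCS and HADS are handed out after the screening pain tests, so the scores, mainly PCS, may partly reflect the test experience rather than pre-existing psychological vulnerability

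*Protocol*

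**What the plan says.** The Protocol, General procedure, introduces its lists with "The screening and study days will proceed as follows", so the bullets read as a sequence. For the screening day:

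1. oral information;
2. medical history, eligibility check and basic measurements;
3. familiarisation, in which "the 3 types of pain conditioning test are presented and performed on the study participant", meaning brief thermal sensitisation (BTS), heat pain detection threshold (HPDT) and long thermal stimulation (LTS);
4. "Distribution of PCS and HADS (in Danish"), with an opaque envelope for the answers and return on the first study day;
5. answers to remaining questions.

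The instrument sections set only an upper time limit: "The PCS questionnaire is to be completed before study day 1" and "The HADS questionnaire is to be completed before study day 1". Under Secondary outcomes the scores are predictors: "To evaluate how precise the scores of PCS and HADS, total and sub-scores, predict the size of the area of secondary hyperalgesia". The Aim and the background section on psychological vulnerability describe this as an association between area and the participant's psychological vulnerability or characteristics.

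**The concern.** PCS asks about rumination, magnification and helplessness in relation to pain. A participant who has just been through three heat-pain procedures may answer differently from one who has not, and the shift may depend on how he responded. The same stimuli recur on study days 1 to 4, and the Aim expects the hyperalgesia response to be reproducible within a person. A score that has absorbed part of the screening response could therefore correlate with the later areas even if vulnerability before any testing had no relation to them.

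The interpretation of one secondary outcome is at stake. An association could be reported as reflecting a pre-existing trait when part of it reflects the test experience. The sealed envelope does not help, because it keeps the scores from the investigators and does nothing about the participant's own prior exposure.

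**Working it through.** **Order of events.** No stated figure is involved, so there is nothing to reproduce. Setting the sections side by side:

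| Event | Where stated | Timing |
|---|---|---|
| BTS, HPDT and LTS performed | General procedure, screening day | before hand-out of the forms |
| PCS and HADS handed out | General procedure, screening day | next bullet |
| PCS and HADS completed | PCS and HADS sections | any time before study day 1 |
| Sealed envelope returned | General procedure, study days | study day 1 |
| Areas of secondary hyperalgesia that are analysed | Primary outcome; General procedure | study days 1 to 4 |

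The scores fall after the first exposure and before every analysed area. Nothing in the Protocol has the forms completed before the exposure, or allows for the exposure in the analysis.

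**Illustration of size.** The documents give no information on how far the scores react, so this is hypothetical.

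Inputs:
- n = 50 (Aim).
- Ratio of intra- to inter-individual variance, 0.25. Sample size estimation says it may exceed 25%, so 0.50 is also tried.
- Outcome taken as the mean area over four days.
- True relation between trait score and area: none (assumed).
- Share of score variance that mirrors the screening area: 2%, 5% or 10% (assumed; zero is also possible).

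With ratio 0.25 the between-person share of variance is 1/1.25 = 0.80 and the within-person share is 0.20. The correlation of one screening response with the four-day mean is 0.80 / sqrt(0.80 + 0.20/4) = 0.80 / 0.922 = 0.868. The induced correlation is sqrt(share) × 0.868. The chance of p < 0.05 follows from Fisher's z with standard error 1/sqrt(47).

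| Share of score variance | sqrt(share) | Induced r | Chance of p < 0.05, unadjusted |
|---|---|---|---|
| 2% | 0.141 | 0.12 | 14% |
| 5% | 0.224 | 0.19 | 27% |
| 10% | 0.316 | 0.27 | 49% |

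A simulation of 20,000 replicates, set by the correlation c between score and screening response instead of by share, gives the same pattern. For c = 0.1, 0.2, 0.3 and 0.4 the rejection rates are 9%, 22%, 46% and 71% at ratio 0.25, and 9%, 18%, 37% and 59% at ratio 0.50. With c = 0, as when the forms are completed first, the rate is about 5%.

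**Two corrections, both downward.**

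- *Felt pain is not the area.* The table treats the experienced response as the mapped area itself. If the scores react to felt pain, and felt pain correlates 0.3 to 0.5 with area (assumed), each induced r is multiplied by that factor. For a 10% share it becomes 0.274 × 0.3 = 0.08 to 0.274 × 0.5 = 0.14. The unadjusted rates fall to about 6–7%, 7–10% and 9–16%.
- *Multiplicity.* The Plan of statistical analysis sets a family-wise error rate of 0.05 with single-step adjustment. Taking Bonferroni over seven scores (PCS total and three sub-scores, HADS total and two sub-scores; the family is my assumption), the per-test level is 0.05/7 = 0.007. The table's correlations then give about 3%, 9% and 22% per test. Adjustment lowers the rates but does not remove an induced correlation.

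**The case against.** The strongest objection is that the planned analysis is still valid for its stated target. The secondary outcome asks how precisely the scores predict the area, and the plan reports prediction errors and 95% prediction intervals. A score collected before the outcome is a legitimate predictor even if familiarisation partly shaped it. This stands. The difficulty arises when the result is read as pre-existing psychological vulnerability, or as the performance of the questionnaires in people not yet tested.

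Second, the outcome is an area mapped with a monofilament, not pain intensity. Participants would more plausibly react to how painful the heat was. Whether HPDT and LTS responses predict area is itself a question of this study, so the felt response cannot be presumed a close proxy for the area. The Clinical evaluations section makes mapping part of BTS, but the screening list does not say separately that it is done. This also stands, and it makes the table above an upper-end illustration.

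Third, the Protocol describes HADS as covering symptoms of anxiety and depression, not thoughts about pain. A brief familiarisation is less likely to move it, and the point applies mainly to PCS.

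Fourth, the reverse order is not neutral. Completing the forms shortly before a first heat-pain test could raise anticipatory anxiety, chiefly in HADS-A, and it gives up completion away from the clinic. This is a real cost but a small one.

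None of this answers the basic observation that the listed order opens a route of contamination that a different order would close.

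**Conclusion.** The point holds as a cheap improvement. As the Protocol is written, PCS and HADS are answered after exposure to the stimuli used for the outcome. The scores, mainly PCS, may partly reflect the reaction to that exposure, and this would weaken a reading of any PCS/HADS-area association as pre-existing vulnerability.

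A reader might infer reverse causation from the outcome. The documents do not support that: every analysed area is measured from study day 1 onwards, after the forms are due, and the only route is indirect, through a screening response that is not analysed. A reader might also take the 14%, 27% and 49% as the expected false-positive rates of the study. They are not. They rest on shares with no source in the Protocol, equate the felt response with the mapped area, assume an effect in one direction, and ignore the planned multiplicity adjustment. The true size and direction are unknown and may be nil.

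The primary variance-component outcome is unaffected, and so is the use of HPDT and LTS as predictors.

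**What to change.** Change the order within the screening visit. After consent, at the start of the visit, participants complete PCS and HADS and seal the envelope, and only then undergo the familiarisation tests. Amend the PCS and HADS sections to require completion before the screening pain tests, not merely before study day 1.

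The cost is 27 items (13 + 14) completed on site instead of between visits, with no extra staff, visit or procedure. Placing the forms at the very start of the visit limits anticipatory anxiety. What remains should be kept in mind when HADS-A is interpreted.

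If screening is already complete, report the order as a limitation and do not describe the scores as free of prior exposure to the tests.

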# **Clinical evaluations**

**Pain assessment**

Visual analogue scale (VAS), index from 0-100 mm, where 0 mm represents “no pain”, and 100 mm represents “the worst pain imaginable”.

**Brief Thermal Sensitization (BTS)**

A computer-controlled thermode (Somedic MSA Thermotester^TM^; size 2.5x5 cm) is placed on the participant’s skin, and the skin is heated to 45°C for 3 min. After 3 min., while the thermode still has contact with the skin, the assessment of secondary hyperalgesia is conducted.

**Assessment of secondary hyperalgesia**

The area of secondary hyperalgesia is quantified after stimulation with a 19G monofilament (von Frey hair) in 4 linear paths arranged in 90° around the centre of stimulation. Stimulation will begin 15 cm. from the centre of stimulation and advance in steps of 5 mm. with 1 second intervals towards the centre of stimulation. When the participant states a clear change in sensation the place will be marked with a felt pen and the transverse and longitudinal axes will be measured for later area calculation.

**Long Thermal Stimulation (LTS)**

The computer-controlled thermode is placed on the participant’s skin, and the skin is heated to 45°C for 1 min. During this the participant evaluates the pain with an electronic VAS-scale. The participant will continuously evaluate the pain using the electronic VAS-scale because of the fluctuations in pain intensity during this type of stimulation. The equipment automatically calculates a VAS-score under the curve (VAS-AUC) and a maximum VAS score for the time period. The participant will not be able to see the computer screen during the measurement, and each pain evaluation will be independent of the previous evaluation.

**Heat Pain Detection Threshold (HPDT)**

Heat pain detection threshold represents the lowest temperature that is perceived as painful, when heating the skin with the computer-controlled thermode. The initial temperature is 32°C, and temperature is increased 1°C/sec. The participant is asked to press a button when the heat is perceived as painful. If 52°C (the maximum temperature for the thermode) is reached before the participant’s threshold has been registered, the thermode will automatically return to the initial temperature of 32°C. The HPDT is calculated as an average of four stimulations. Each stimulation will be performed with an interval of 6-10 seconds.

**Hospital Anxiety and Depression scale (HADS)**

HADS is a questionnaire consisting of 14 questions, and is a 4-point Likert scale with values from 0-3. HADS can be subdivided into HADS-A, evaluating anxiety, and HADS-D, evaluating depression. The highest achievable score is 42, and a total HADS-score will estimate the participant’s level of distress. To evaluate anxiety and depression separately, HADS-A and HADS-D must be evaluated separately, with a maximum score of 21 in the two subtests (20).

The interpretation of the score in HADS-A and HADS-D is as follows:

- 0-7: Normal
- 8: Mild level of anxiety/depression
- 11-15: Moderate level of anxiety/depression
- >16: Severe level of anxiety/depression

The HADS questionnaire is to be completed before study day 1.

**Pain Catastrophizing Scale (PCS)**

PCS is a questionnaire consisting of 13 questions. PCS is a 5-point Likert scale with values from 0-4, and can be subdivided into 3 subtests, that each evaluates the central elements in catastrophizing: Rumination, magnification and helplessness. The highest achievable score is 52, and with separate evaluation of the three subtests, the 3 different elements can be assessed individually. To evaluate the 3 elements separately the 13 questions must be evaluated in the 3 following subgroups:

- Rumination: The sum of question 8, 9, 10, 11. Maximal sum =16
- Magnification: The sum of question 6, 7, 13. Maximal sum = 12
- Helplessness: The sum of question 1, 2, 3, 4, 5, 12. Maximal sum = 24

The PCS questionnaire is to be completed before study day 1.

# **ADVERSE EFFECTS**

## **Adverse effects/adverse events (AEs)**

Any adverse event, signs or symptoms that occur during participation in the study, which are time related to study procedure, whether the adverse event is considered to be related to the study procedure or not will be registered in the study participant’s Case Report Forms. If an adverse event occurs more than 48 hours after the last procedure of the trial, and there is no apparent causal connection or relation to the study procedure, this shall not be deemed to be an adverse event.

Start and end date/time, severity and effects after the study procedure must be recorded for all incidents. The severity of the adverse event and the relationship with the study procedure must be assessed in accordance with the guidelines described below.

